**Figure 1 F1:**
[figure not shown]
Illustration of Estimated Study Power.

### Recruitment

#### Recruitment of hospitals

All 24 hospitals have been approached and have consented to participate in our study.

#### Recruitment of families to complete prospective survey

As of Oct. 27^th^, 2002 we have recruited a total of 170 children into our baseline cohort and 95% have been contacted daily until resolution of symptoms. We will continue to recruit patients until April 30^th^, 2003. Given our rate of enrolment to date, we anticipate enrolling between 450 and 500 patients in the baseline cohort. The intervention and follow-up sample will be obtained over a total of 24 months, as opposed to the baseline in which we will have enrolled patients for only 13 months. Therefore, conservatively, enrolment should be ~ 900 patients in the follow-up cohort.

### Practical arrangements for allocating participants to trial groups

#### Proposed strata, rationale and method of allocation

As noted above, a total of 24 hospitals have agreed to participate in our study. We will stratify these hospitals into three levels based on the average number of croup cases diagnosed by affiliated physicians per year *(< 100 cases/year = small volume hospitals; 100 to 700 cases per year = medium volume hospitals, and > 700 cases per year = large volume hospitals)*. Non-stratified randomization of only 24 hospitals into three intervention arms could easily result in substantially more hospitals of one stratum in one intervention arm than the other arms. Therefore, given the significant differences in total number of disease episodes, number of hospitalizations, hospitalization rates, and likely other significant differences between the different sized hospitals, non-stratified randomization could significantly bias our results. A statistician not otherwise involved in our study will randomise hospitals within each of the three strata to one of the three intervention arms by computer software.

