#### BaselineUtilisation data from Alberta

Utilizing provincial administrative data, we have established health care utilization rates including the a) number of disease episodes, b) number of physician visits per disease episode, and c) number of hospital admissions and hospitals days per disease episode, for children with croup in Alberta for 6 years. Among the 107 Alberta hospitals, we found up to an 18 fold range in hospital admissions rates, ranging from16 to 287/1000 disease episodes. In general, those hospitals that evaluated larger numbers of children with croup had lower utilization rates. For example, the six largest volume hospitals diagnosed a total of 86,711 cases, and averaged 21 hospital admissions/1,000 disease episodes; and the 30 smallest volume hospitals diagnosed 13,750 cases and averaged 116 hospital admissions/1,000 disease episodes.

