## Methods

### Proposed trial design

We will conduct a cluster randomized controlled trial after completing a baseline survey. In order to provide a comprehensive answer as to whether or not our interventions are beneficial, we have obtained data from several different sources. The stages are as follows.

1. Baseline survey (currently near completion):

▪ Utilizing administrative data, we have documented Alberta health care utilization rates.

▪ We are documenting severe adverse outcomes in Alberta utilizing administrative data, and both medical examiner and records audit.

▪ Using this data, we have rank ordered Alberta hospitals based on number of disease episodes and rates of hospitalization.

▪ We have enrolled the highest ranking 24 hospitals who consented to participation.

▪ We are documenting practice patterns in these 24 selected Alberta hospitals utilizing medical records audit.

▪ Utilizing a prospective cohort questionnaire, we are documenting the duration of clinical symptoms of children with croup and the psychosocial burden on their families in the same 24 selected Alberta hospital emergency departments

2. Development of clinical guidelines that address indications for drug therapy and hospital admission/discharge criteria. The process will include:

▪ convening an guideline committee with a range of disciplines and professions;

▪ critically reviewing the published literature;

▪ drafting guidelines which meet standard criteria for developing guidelines;

▪ review of the guidelines by both parents and a wide-range of users (family physicians, nurses, and respiratory therapists);

▪ obtaining approval of the guidelines from the Canadian Pediatric Society, Canadian Association of Emergency Physicians, and the Alberta Medical Association; and

▪ publishing the guidelines in journals such as the Canadian Medical Association Journal.

3. Randomization of 24 Alberta hospitals to one of three implementation strategies.

4. A follow-up survey whose purpose is to detect any change from baseline by:

▪ documenting severe adverse outcomes and utilization rates in Alberta;

▪ documenting practice patterns in the 24 Alberta hospitals surveyed at baseline;

▪ documenting the duration of symptoms of children with croup and the psychosocial burden on their families attending these 24 hospital emergency departments.

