### Proposed sample size

The twenty-four participating hospitals were initially selected by calculating anticipated hospital specific effect sizes based on assuming that the effect of intervention would be proportional to baseline admission rates taking into account hospital-specific frequencies of disease episodes. Hospitals are to be randomized to one of three intervention arms, eight hospitals per arm, after stratification on baseline frequency of disease episodes. The power of our study depends on the anticipated change in mean hospital days as shown in Figure 1, which provides power estimates plotted against percentage decrease based on examining hospital stays over the three baseline and three post-intervention years. (Appendix A – Details of calculations) A Bonferroni correction for the two comparisons of intermediate and high intensity intervention against low intensity intervention has been included. The estimated power (overall alpha = .05) to detect a 25% change is 0.80 for each comparison.

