#### Identification & enrolment of participating hospitals

As noted above, Alberta hospitals were rank ordered based on the number of disease episodes and rates of hospitalization for a six-year period. We then approached in this order each of the hospital administrators and clinical staff for permission to include their hospital in our study until a total of 24 hospitals consented (the staff of 11 hospitals refused to participate for reasons ranging from "anticipated closing of the hospital in the near future" to "too heavy an administrative workload to participate in a study").

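### Allocation is balanced on case volume only, although each hospital's baseline hospital-day rate is known beforehand and the plan expects the effect to scale with the baseline admission rate

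*Protocol article*

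**What the plan says.** Two sections fix the allocation, and they agree. *Proposed sample size*: "Hospitals are to be randomized to one of three intervention arms, eight hospitals per arm, after stratification on baseline frequency of disease episodes". *Proposed strata, rationale and method of allocation*: "We will stratify these hospitals into three levels based on the average number of croup cases diagnosed by affiliated physicians per year", with bands below 100, 100 to 700, and above 700 cases a year. An independent statistician "will randomise hospitals within each of the three strata to one of the three intervention arms by computer software". Neither section states matching, minimisation or any constraint on the hospitalization rate. The abstract speaks of a matched pair trial, but the Methods describe no matching.

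The baseline rate is known and is treated as important elsewhere:

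- The baseline utilisation section reports six years of admissions and hospital days per episode.
- *Identification & enrolment of participating hospitals*: "Alberta hospitals were rank ordered based on the number of disease episodes and rates of hospitalization for a six-year period".
- *Recruitment of hospitals*: all 24 have consented, so the full list exists before allocation.
- *Proposed sample size* selected hospitals by "assuming that the effect of intervention would be proportional to baseline admission rates".
- The allocation section justifies stratifying "given the significant differences in total number of disease episodes, number of hospitalizations, hospitalization rates" and other differences between hospitals of different size.

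*Proposed analyses* gives a linear mixed model over baseline and study years, with random hospital and year-within-hospital effects and fixed effects for intervention and year. It names no baseline-rate covariate. The cost analysis does use baseline cost as a covariate.

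**The concern.** The primary outcome is hospital days per 1,000 episodes. The sponsor already holds six years of it for each hospital and expects the intervention effect to depend on the admission rate behind it. Three volume bands balance that rate only as far as volume predicts it. With eight hospitals per arm, the rest is left to chance.

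This matters because some change is likely to be common to all arms: the guideline is mailed to every registered physician in the province and is to be submitted for journal publication. If that change is proportional, it is larger in absolute terms where the baseline is higher. An arm that happens to draw high-rate hospitals would then show a larger absolute fall with no difference between strategies. Including baseline years removes the difference in level, not this difference in change. Once hospitals are allocated, the design can no longer prevent it.

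**Working it through.** **The plan's own figure.** The stated power is 0.80 for a 25% change, with overall alpha 0.05 and Bonferroni for two comparisons. The calculation appendix and Figure 1 are not shown, so it cannot be reproduced, only solved backwards. With 8 hospitals per arm and two-sided 0.025 (sidedness assumed), the implied standard error of the arm difference is 0.25 / (2.241 + 0.842) = 0.081 of the mean. This neither confirms nor refutes the 0.80.

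**Inputs from the article.**
- Range over all 107 hospitals: "we found up to an 18 fold range in hospital admissions rates", 16 to 287 per 1,000 (287/16 = 17.9).
- Six largest hospitals: 21 per 1,000, and 86,711/(6 × 6) = 2,409 cases each a year.
- Thirty smallest: 116 per 1,000, and 13,750/(30 × 6) = 76 cases each a year.
- Rate ratio between these groups: 116/21 = 5.5. Volume therefore carries much of the rate gradient.
- Six large-volume hospitals are in the trial.

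**Assumptions.**
- Strata of 12 small, 6 medium and 6 large hospitals; the article gives no full split.
- Medium-stratum mean of 60 per 1,000.
- Log-normal spread within strata with log-SD 0.2 to 0.6, and rates kept within 16 to 287.
- Unweighted arm means of admission rates, standing in for hospital days.

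For scale, 107 log-normal values have an expected log range of about 5.06 SD, so 17.9-fold implies a total log-SD of ln(17.9)/5.06 = 0.57. A within-stratum value of 0.6 is therefore a ceiling.

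**Simulation.** The quantity is the larger over the smaller arm mean baseline rate for one planned pair (intermediate or high against low). There were 250 sets of rates per setting and 200 stratified allocations per set. The best tenth was scored on the spread of the three arm mean rates.

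| log-SD | Volume strata: median | above 1.25 | above 1.5 | Best 10%: median | Triplets: median |
|---|---|---|---|---|---|
| 0.2 | 1.08 | 5% | 0% | 1.02 | 1.04 |
| 0.3 | 1.12 | 19% | 2% | 1.03 | 1.06 |
| 0.4 | 1.17 | 33% | 8% | 1.04 | 1.07 |
| 0.5 | 1.21 | 42% | 14% | 1.06 | 1.10 |
| 0.6 | 1.25 | 51% | 22% | 1.07 | 1.12 |

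Splits of 9/9/6 and 6/12/6 (small/medium/large) give medians within 0.01 of these for volume strata. At log-SD 0.4, medium-stratum means of 40 and 90 give the same 1.17.

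**What a gap does on the linear scale.** The mean over 24 hospitals is (12 × 116 + 6 × 60 + 6 × 21)/24 = 78 per 1,000. A pair at ratio 1.25 around it starts at about 87 and 70. A common 20% fall (assumed) removes 17.4 and 13.9, a difference in change of 3.5 per 1,000. A 25% effect is 0.25 × 78 = 19.6, so 3.5 is about 18% of it.

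**Against the implied standard error.** At log-SD 0.4 the relative baseline difference for a pair has SD 0.227. Under the same 20% fall this adds 0.20 × 0.227 = 0.045 of the mean, and (0.045/0.081)² is about 0.31 of the implied variance. The best-tenth draw has SD 0.061, giving 0.012 and about 0.02. The share goes with the square of the fall: at 10% it is a quarter as large.

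**The case against.** Several points on the other side stand.

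*Volume is the plan's answer to rate imbalance.* The allocation section lists hospitalization rates among things that differ between hospital sizes, and the 21 against 116 contrast bears it out. A reader might infer that the plan names rates and then ignores them; the text does not support that.

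*The size is uncertain.* The 18-fold range covers 107 hospitals. The 24 were chosen partly on rate, so their spread may be narrower. At log-SD 0.2 a gap above 1.25 is rare.

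*The planned contrasts are pairs.* Comparing the highest with the lowest of three arms gives larger figures (medians 1.13 to 1.47 over the same range). A reader might infer from them that arms will start far apart, but the plan tests two strategies against low intensity, so the pairwise figures apply.

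*On a percentage scale the problem goes away.* The power statement is in percentage decrease, and a common 20% fall is 20% in every arm. But the named model is linear, so the absolute difference remains under the analysis as written.

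*Bias and regression to the mean.* A reader might infer systematic bias, or a false effect from picking high-rate hospitals. Neither is supported. Stratified randomisation is valid, and selection used 1994 to 2000 data. Three further baseline years precede the August 2003 start, so most regression should be over by then.

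Finally, the simulation uses unweighted admission rates, while the model works on stays from individual episodes. It shows the order of size, not the exact imbalance.

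**Conclusion.** The point holds as a cheap improvement, not as a flaw that invalidates the design. Balance on the baseline rate is partial. For one planned comparison the median ratio of arm means is about 1.08 to 1.25, and it exceeds 1.25 in about 5% to 50% of allocations. A constrained draw brings the median to about 1.02 to 1.07. These figures rest on an assumed spread, an assumed stratum split and admissions in place of hospital days. They also treat the rate as stable, so the gain is an upper bound if rates drifted after 2000. The cost of leaving it is precision and credibility, because the linear model does not absorb a shared proportional change. The sponsor holds the actual rates and can replace the assumed range at once.

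**What to change.** Before allocation, keep the three volume strata and let the independent statistician do one of the following:

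- List or sample stratified allocations, score each on arm mean baseline hospital days per 1,000 episodes and arm total episodes, and draw at random from the best-balanced set, for example 10%.
- Order hospitals by baseline rate within strata and randomise within triplets.

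Randomness remains ample: under a 12/6/6 split there are 12!/(4!)³ × 90 × 90 = 280,665,000 stratified allocations, so a tenth is about 28 million.

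In the analysis, respect the constraint in one of two ways. Either model the post-allocation years with the baseline rate as covariate, as the cost analysis does, or use a permutation test over the constrained set. A baseline main effect added to a model that also has baseline years as outcomes would not capture differential change. Correct the matched pair label in the abstract to fit whichever scheme is used.

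The cost is a little programming before allocation and an analysis tied to the constrained set. No extra data are needed.

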**Methods/designs:**

We propose to use a matched pair cluster trial in 24 Alberta hospitals randomized into three intervention groups. We will use mixed methods to assess outcomes including linkage and analysis of administrative databases obtained from Alberta Health and Wellness, retrospective medical chart audit, and prospective telephone surveys of the parents of children diagnosed to have croup. The intervention strategies to be compared will be mailing of printed educational materials (low intensity intervention), mailing plus a combination of interactive educational meetings, educational outreach visits, and reminders (intermediate intensity intervention), and a combination of mailing, interactive sessions, outreach visits, reminders plus identification of local opinion leaders and establishment of local consensus processes (high intensity intervention). The primary objective is to determine which of the three intervention strategies are most effective at lowering the rate of hospital days per 1,000 disease episodes. Secondary objectives are to determine which of the three dissemination strategies are most effective at increasing the use of therapies of known benefit. An economic analysis will be conducted to determine which of the three intervention strategies will most effectively reduce total societal costs including all health care costs, costs borne by the family, and costs stemming from the strategies for disseminating guidelines.

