### Proposed analyses

The principal analysis will examine hospital stays arising from individual disease episodes over the six-year baseline and study period. We will apply a linear mixed model (Laird-Ware approach) incorporating random effects for hospital, year within hospital, as well as fixed effects for intervention and year. We will also pursue a more detailed explanatory analysis incorporating individual subject characteristics (age, sex) as well as random effects for admission and discharge physician. Additionally we will develop similar models for length of stay restricting to disease episodes leading to admissions, and mixed effects logistic regression model for admissions. Secondary analyses relating to steroid use and *Telephone OutPatient (TOP) *scores will follow a similar format. The examination of day 1- 3 *TOP *scores will require augmenting the basic model framework to include random subject effects and a serially correlated (within subject) residual error structure. No subgroup analyses are planned.

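### Hospitals are randomised within three volume strata, but the listed terms of the principal model omit stratum, and the abstract calls the design matched pair

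*Protocol article*

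**What the plan says.** Under the heading on strata and method of allocation, the protocol article forms three levels of hospital by annual croup cases (below 100, 100 to 700, above 700). An independent statistician "will randomise hospitals within each of the three strata to one of the three intervention arms". The sample size section agrees: "eight hospitals per arm, after stratification on baseline frequency of disease episodes". The reason given for stratifying is prognostic: "given the significant differences in total number of disease episodes, number of hospitalizations, hospitalization rates".

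Under Proposed analyses, "The principal analysis will examine hospital stays arising from individual disease episodes over the six-year baseline and study period". The model is a linear mixed model "incorporating random effects for hospital, year within hospital, as well as fixed effects for intervention and year". The explanatory version adds age, sex and physician effects. The secondary analyses of steroid use and telephone symptom scores are to take a similar form. The cost model, under Calculation of societal costs, names baseline cost as its covariate. None of these lists volume stratum.

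The abstract describes the design differently: "We propose to use a matched pair cluster trial in 24 Alberta hospitals randomized into three intervention groups".

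**The concern.** A factor used to restrict randomisation normally belongs in the analysis. Stratified allocation balances the arms on volume, so the true sampling variance of an arm contrast excludes variation between strata. A model without stratum can still count that variation in its standard error. The interval is then too wide, the test rejects too seldom under the null, and power falls. With only 24 clusters there is little to spare.

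The strata are plausibly strong predictors. In the provincial baseline data, "the six largest volume hospitals diagnosed a total of 86,711 cases, and averaged 21 hospital admissions/1,000 disease episodes", while the 30 smallest hospitals averaged 116 per 1,000.

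The design label is a separate, simpler matter. Pairs cannot be allocated to three arms, and no pairing appears in the sample size, allocation or analysis sections.

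**Working it through.** **1. How prognostic the strata are.** The baseline covers six years.
- Six largest hospitals: 86,711 / 6 / 6 ≈ 2,409 cases a year each, in the large stratum; 21 admissions per 1,000.
- Thirty smallest: 13,750 / 30 / 6 ≈ 76 a year each, on average in the small stratum; 116 per 1,000.
- Ratio: 116 / 21 ≈ 5.5.

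These are admissions among all Alberta hospitals, not hospital days in the 24 trial hospitals, so they serve only as a proxy.

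**2. The plan's own power.** The sample size section states 0.80 for a 25% change, with Bonferroni correction for two comparisons (0.025 each, two-sided assumed). No SD or intraclass correlation is in the text at hand, so 0.80 cannot be reproduced forwards. Backwards, with 8 hospitals against 8:
- required effect/SE = 2.241 + 0.842 = 3.083
- SE = 0.25 / 3.083 = 0.0811
- SD of relative change = 0.0811 / √(2/8) = 0.162 (0.152 with t on 21 df)

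The 0.80 therefore implies a hospital-level SD of about 0.15 to 0.16. Nothing shown says whether that is right.

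**3. Effect estimated as change (arm by period).** Simulation of hospital-year means with a random hospital intercept: 24 hospitals, 8 per arm, six baseline and three study years. Assumed: strata of 6/9/9 hospitals (only the 6 is documented), stratum means 21/65/116 (65 assumed), within-stratum log-SD 0.4. Year-to-year noise was set so that power lay near 0.80; 600 runs per setting.

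| Setting | No stratum | Stratum | Stratum and stratum × period |
|---|---|---|---|
| Additive effect, no trend | 0.833 | 0.835 | not run |
| Proportional effect, assumed 20% secular fall | 0.830 | 0.842 | 0.860 |

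In the first row the mean SE is 5.55 without and 5.53 with stratum. In the second the full gain is 0.860 − 0.830 = 3 points. In a noisier setting (400 runs), where power without stratum was only 0.422, the proportional case rose to 0.455 and 0.472, a gain of 5 points. Null rejection in the table's settings lay between 0.018 and 0.027 against a nominal 0.025.

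Stable level differences fall into the hospital effect and cancel in the change. What remains arises when changes are proportional to baseline but modelled additively, since absolute change then differs by stratum.

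**4. Effect estimated as a constant arm term over all years.** Same set-up with the noisier, no-trend variance, 400 runs under the null:
- without stratum: mean model SE 25.7 against a true SD of 17.0 (25.7 / 17.0 ≈ 1.5); null rejection 0.000
- with stratum: mean model SE 16.8; null rejection 0.028

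Stratum repairs the standard error but not the model. Three study years in nine dilute the effect to about a third, and power for a 25% effect was 0.000 without and 0.028 with stratum.

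**5. Formula for a comparison of levels.** Let R² be the share of between-hospital variance that the strata explain, and suppose the adjusted analysis has power 0.80. The unadjusted SE is too large by 1/√(1 − R²), so power ≈ Φ(3.083 − 2.241/√(1 − R²)).

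| R² | 0.05 | 0.10 | 0.20 | 0.30 | 0.50 |
|---|---|---|---|---|---|
| Power without stratum | 0.783 | 0.764 | 0.718 | 0.657 | 0.465 |

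A version with t critical values gives 0.80, 0.78, 0.73, 0.66 and 0.46.

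**The case against.** The strongest reply is that the model already does most of the work. It uses baseline and study years of the same hospitals with a random hospital effect, and the primary objective, the purpose of the follow-up survey and the power statement all speak of change from baseline. On that reading the 5.5-fold difference in level largely cancels. This stands, and it is why the likely loss is small. What does not cancel is stratum-specific change. The sample size section itself assumes intervention effects proportional to baseline admission rates, while the principal model is linear. The analysis section also never says whether intervention enters as an arm-by-period or a constant arm term.

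It can also be said that a condensed article need not list every covariate, and that its list is not declared complete. That is fair. But the article does set out the principal model's random and fixed effects, so the stratification factor should be among them.

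Stronger readings are tempting but unsupported:
- That the stated power is wrong, or that power is certainly lost: no variance components are available to show either.
- That the benefit of stratifying is thrown away: the stated purpose is to prevent imbalance between arms, and stratified allocation achieves that whatever the model.
- That an invalid paired analysis is intended: a mixed model is planned, and the label is a wording error in the abstract.

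**Conclusion.** The point holds in a limited form. Randomisation is stratified on a factor that the protocol treats as prognostic, the listed terms of the principal model omit it, and the abstract's label contradicts the body. The omission causes neither bias nor excess false positives; any error is in the conservative direction.

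Under the change-from-baseline reading, which the rest of the document favours, the cost is about 0 to 3 points when power is near the planned level. It is greatest when changes are proportional but modelled additively, and somewhat more in the noisier setting. Under a comparison of levels it could be large, for example 0.80 falling to 0.66 if the strata explain 30% of the variance. The hospital mix, medium-stratum rate, variances and secular fall are all assumptions. The label contradiction and the missing term depend on none of them.

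**What to change.** - Add volume stratum (three levels) as a fixed effect, with stratum by period, to the principal model and to the similar secondary and cost models. Where baseline is already a covariate, as in the cost model, the stratum main effect does most of this work.
- State that the intervention effect is the arm-by-period term, that is, the difference between arms in change from baseline.
- In the abstract, replace the matched pair label with stratified cluster randomised trial.

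The cost is analysis wording and a few degrees of freedom. Stratum uses 2 (21 to 19 at hospital level). If the strata explain nothing, power falls from 0.800 to 0.794, about 0.6 points. Stratum by period brings the total to at most 4. No change to allocation or data collection is needed.
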